#### Analyses

Differences in baseline characteristics (e.g., demographic factors and outcome measures) of residents in the intervention and control site(s) will be investigated using independent samples t-tests. Any differences identified may be considered as covariates in the main analyses. We will attempt to control for any unusual events and socio-economic or political influences that occurred during the study period. Covariates may include age, gender, building site, functional ability, car ownership, socio-economic status or other demographic variables that differ between residents of intervention and control sites at baseline.

We intend to run a difference-in-difference analysis to test for differences between intervention and control groups in change from baseline to 3-6-month post-move-in, and change from baseline to 9-12-month post-move-in. The type of analysis will depend on the measurement unit of each outcome (e.g., linear regression for continuous outcome variables, logistic regression for categorical outcome variables). For the primary outcome of PA, a difference-in-difference linear regression analysis with a continuous outcome will have 80 % power with 107 participants for a model with five main predictor variables and three covariates at α = 0.05 [53].

Depending on how many units the final intervention and control sites have, data may be collected on couples and a multi-level modeling approach used to control for clustering within unit. The approach that is best able to maximize power will be chosen.

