#### Measures

***Physical activity***: Objective measures of PA will be obtained using Actigraph wGT3X-BT accelerometers (Actigraph LLC, Pensacola, FL). Decision rules will follow recommendations of Migueles, Cadenas-Sanchez [40] for use with Actigraph accelerometers. Data will be collected in 60 s epochs with a sampling frequency of 60 Hz and the normal filter. Non-wear-time will follow the Choi, Liu [41] algorithm. Days of PA measurement will be considered “valid” if the device is worn for 10 or more hours per day. Four or more days of wear is considered a “valid” measurement week. The main outcomes of interest are average steps per day, minutes of total PA per day, and minutes of moderate-to-vigorous PA (MVPA) per day.

Participants’ location will be tracked using Qstarz BT-Q1000XT Travel Recorder XT GPS devices. These are satellite-based global navigation systems that measure participants’ location every five seconds. A “valid” measurement week will be considered four or more days of wear. Exact GPS variables are still being finalized but will likely include transport and leisure walking. We plan to use the HABITUS software [42] to merge and process accelerometer and GPS data.

To supplement GPS and accelerometer measurements, participants will also complete a travel diary and logbook. They will record their wake and bedtimes, and times when the devices are taken off, and details on where they travel.

Self-report measures of leisure and transport PA from the past seven days within the neighbourhood will be measured using the Neighbourhood – International Physical Activity Questionnaire (N-IPAQ)[43]. Self-reported stair climbing will be assessed with the question “How many total floors of stairs throughout the day do you walk UP on an average weekday at your CURRENT home building?” (responses: 0 floors, 1–2 floors, 3–6 floors, 6 or more floors, unable to walk up the stairs).

***Dietary assessment***: Frequency of fruits and vegetable, salty food, and sugar-sweetened beverage consumption will be assessed using a food frequency questionnaire adapted from the Nutritional Environment Measures Survey – Perceived Nutrition Environment (NEMS-P)[44].

***Social connections***: Connections to people in one’s neighbourhood will be captured using survey questions of sense of belonging [45], community satisfaction [46], local social ties [47], and social cohesion and trust [48].

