***Capability, Opportunity, and Motivation***: Physical opportunity will be assessed as perceptions of healthy food access in the neighbourhood using the NEMS-P [44]. Items will assess access to stores and restaurants, store availability of healthy food choices, store prices of fruits and vegetables, store placement of healthy items and nutrition information, availability of healthy options at restaurants, restaurant promotion of healthy options and nutrition information, and costs of healthy options at restaurants.

Physical opportunity will be assessed as perceptions of neighbourhood supports for PA using the Physical Activity Neighbourhood Environment Scale (PANES)[49]. This scale captures residential density, land mix use, street connectivity, proximity to neighbourhood recreation facilities, pedestrian infrastructure, bicycling infrastructure, aesthetic qualities, social cues for PA, traffic and crime safety, and access to a working automobile.

Physical capability around PA will be assessed using two questions from the short form health survey (SF-12)[50]. Two questions on functional limitations ask “Does your health now limit you in these activities? If so, how much?” Activities include (a) moderate activities such as moving a table, pushing a vacuum cleaner, bowling, or playing golf, and (b) climbing several flights of stairs.

Questions on motivation, capability, and social opportunity may be assessed using generic items designed specifically for the COM-B [51]. Specific outcomes included in these questions will be selected based on the final design and amenity intervention elements that are implemented at the site(s). For example, if healthy stairwell design elements are implemented, then stair climbing will likely be included as an outcome.

***Body mass index (BMI)***: Measurements of height and weight will be taken using the Canadian Physical Activity, Fitness and Lifestyle Appraisal procedures [52]. Specifically, body weight in Kilograms (nearest 0.1 kg) and height in meters (nearest 1.0 mm) will be measured twice in each participant with light clothing and no shoes using a portable physician-grade stadiometer and scale (Health o Meter). BMI will be calculated as kg/m^2^.

***Socio-demographic information***: Age, gender, ethnicity, physical and mental health status, marital status, smoking and alcohol use, employment status, income, education, and falls in the past year, will be measured using standard questionnaire items.

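### The t-test is the only test named for baseline differences, and it does not work for nominal factors with three or more categories such as ethnicity, marital status and employment status

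*Protocol article*

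**What the plan says.** In the protocol article, under Quantitative resident evaluation, Analyses, the baseline comparison is described in one sentence. Its scope is "Differences in baseline characteristics (e.g., demographic factors and outcome measures"), and the method is that these differences "of residents in the intervention and control site(s) will be investigated using independent samples t-tests". No other test is given for any type of variable. On how the result will be used, the section says: "Any differences identified may be considered as covariates in the main analyses".

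The list of possible covariates reads: "Covariates may include age, gender, building site, functional ability, car ownership, socio-economic status or other demographic variables that differ between residents". Ethnicity and marital status are not named there.

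The variables concerned are described under Measures in the same part of the article:

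- Socio-demographic items: "Age, gender, ethnicity, physical and mental health status, marital status, smoking and alcohol use, employment status, income, education, and falls in the past year". Response formats are not given. Only age is plainly continuous. Ethnicity, marital status and employment status are nominal.
- Stair climbing, a self-reported outcome: ordered floor counts whose last two answers are "6 or more floors, unable to walk up the stairs".
- The principal physical activity outcomes, which are continuous: "The main outcomes of interest are average steps per day, minutes of total PA per day, and minutes of moderate-to-vigorous PA (MVPA) per day".

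For the outcome models, by contrast, the Analyses section does match method to variable: "The type of analysis will depend on the measurement unit of each outcome", with linear regression for continuous outcomes and logistic regression for categorical ones.

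**The concern.** A t-test compares two means. For a nominal factor with three or more categories there is no mean to compare unless the categories are first given numbers, and the numbers are arbitrary. The p-value then reflects the numbering as well as the data. The stair item has a related problem, because inability to climb has no natural place on a scale of floors climbed.

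This matters because residents are not randomised to sites, so differences in who lives where are the main route to confounding. A demographic factor that is not on the list of possible covariates enters the models only if it is found to differ at baseline. Marital status plausibly bears on social connections, which is a study outcome. If the check cannot see an imbalance in it, the report may call the groups comparable on that factor and leave it out of the adjustment. A different numbering of the same data could lead to the opposite decision.

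**Working it through.** The plan gives no figure for the baseline comparison, so there is nothing to reproduce. The check asks whether the named test can do its job on a nominal factor.

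**Inputs**

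- Total of 107 residents, from the power statement in Analyses.
- Split of 53 and 54: an assumption, since no ratio is stated.
- Two-sided 5% level for the baseline tests: an assumption. The article gives α = 0.05 for the power statement only.
- A three-category nominal factor with counts 22/10/21 in group 1 and 11/32/11 in group 2. These counts are hypothetical. They amount to 42/19/40% against 20/59/20%, which is a gross imbalance.

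**Step 1. t-test with the categories numbered 1, 2, 3**

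- Mean of group 1: (22×1 + 10×2 + 21×3)/53 = 105/53 = 1.98.
- Mean of group 2: (11×1 + 32×2 + 11×3)/54 = 108/54 = 2.00.
- Sums of squares about the means: 42.98 and 22.00. Pooled SD = √((42.98 + 22.00)/105) = 0.787.
- t = (1.981 − 2.000)/(0.787 × √(1/53 + 1/54)) = −0.019/0.152 = −0.12 on 105 df, p = 0.90.

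**Step 2. Same residents, with the first two numbers exchanged (2, 1, 3)**

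- Mean of group 1: (22×2 + 10×1 + 21×3)/53 = 117/53 = 2.21.
- Mean of group 2: (11×2 + 32×1 + 11×3)/54 = 87/54 = 1.61.
- Sums of squares: 28.72 and 34.83. Pooled SD = √(63.55/105) = 0.778.
- t = (2.208 − 1.611)/(0.778 × √(1/53 + 1/54)) = 0.596/0.150 = 3.96 on 105 df, p = 0.00013.

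**Step 3. Chi-square test on the 2×3 table**

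- Expected counts are row total × column total / 107: 16.35, 20.80, 15.85 in group 1 and 16.65, 21.20, 16.15 in group 2.
- Σ(O − E)²/E = 18.31 on 2 df, p = 0.00011. The numbering does not enter.

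**Step 4. Is this one lucky table?** In 20,000 simulated studies of 54 and 53 residents with true shares of 40/20/40% and 20/60/20%, the imbalance was significant at 5% in:

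| Test | Detected |
|---|---|
| Chi-square | 98% |
| t-test, codes 1, 3, 2 | 97% |
| t-test, codes 1, 2, 3 | 4.9% |

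The last figure is the false-positive rate: under that numbering the test has no sensitivity to this imbalance. With four categories (20/7/7/20 against 7/20/19/7) the chi-square test gives p = 0.00002, while the t-test ranges from p = 0.000004 to p = 0.97 over the 24 possible numberings.

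**Step 5. Where the problem stops.** For a binary factor, 34 of 54 against 22 of 53, the t-test and the chi-square test both give p = 0.026. For ordinal items a t-test on scores is defensible. For continuous measures such as steps, activity minutes and BMI the t-test is suitable.

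**The case against.** The other side has several fair points.

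- **Scope.** The sentence does not say that every characteristic, without exception, will be tested this way. A reader might infer that most of the baseline comparison is invalid because most listed items are categorical. The documents do not support that. Many items may be binary or ordinal, response formats are not given, and the main activity outcomes and BMI suit a t-test. This stands, and it confines the point to nominal factors with three or more categories and the stair item.
- **Practice.** The analysts may dichotomise marital status, test indicators one by one, or use a chi-square test without saying so. Either of the first two would also remove the dependence on numbering. This is possible, but the text says none of it. Nor is this a detail left to a fuller plan: the article states a method, and states it for demographic factors by name.
- **Constructed counts.** The example puts the imbalance in the middle-coded category, which is the pattern that hides best. That is true. It shows what can happen, not what is likely here.
- **Other safeguards.** Sites are to be matched as closely as possible, with age and income as resident examples, and age, gender, functional ability, car ownership and socio-economic status are named as possible covariates. So comparability does not rest on the t-test alone. These safeguards do not name ethnicity or marital status.
- **Consequence.** A reader might infer that the adjusted treatment effect will be wrong. The documents do not support that either. Differences found only may be considered as covariates, so the test does not fix the model. In a linear difference-in-difference analysis a stable effect of a factor on the level of the outcome cancels. Bias requires that the factor affects change, which has not been shown.

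**Conclusion.** Wrong as written, minor severity. The one test named for baseline differences does not measure imbalance in nominal factors with three or more categories, although the sentence covers such factors expressly. In the hypothetical example the same data give p = 0.90 or p = 0.0001 by numbering alone, against p = 0.0001 from a test suited to the variable.

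This rests on three assumptions: that ethnicity, marital status or employment status keep three or more unordered levels, that their codes are entered in the t-test as the sentence implies, and that the 107 residents split about evenly. The dependence on numbering does not need the last of these.

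The effect is on the comparability statement and on which unlisted factors come up for adjustment. The power figure and the form of the primary physical activity model are unaffected.

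**What to change.** Replace the sentence with a rule by variable type, for example: continuous baseline characteristics will be compared by independent samples t-tests; categorical characteristics will be compared by their distribution over categories, using the chi-square test or Fisher's exact test where counts are small, or standardised differences by category. Add that a factor with several categories is handled as one set of indicators, in the comparison and if it becomes a covariate, and that the unable answer of the stair item is kept as a category of its own.

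Replacing the t-test by standardised mean differences for continuous variables would be a matter of preference and is not needed to cure this defect.

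The cost is a sentence or two in the analysis section. No new data, measurements or participants are needed.

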## Methods/design

### Study design

The quantitative component will follow a quasi-experimental pre-post design as the assignment to groups is non-random and our research team is working with developers and municipalities to influence the interventions. However, uptake of suggested building and site scale recommendations is ultimately up to the discretion of the developers and architects, and uptake of neighbourhood-scale recommendations is ultimately up to the discretion of the municipalities.

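### Covariates for a non-randomised difference-in-difference are tied to baseline t-tests, and the plan does not make clear that they will act on change, where the remaining confounding lies

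*Protocol article*

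**What the plan says.** The Study design section of the Protocol article is explicit about allocation: "The quantitative component will follow a quasi-experimental pre-post design as the assignment to groups is non-random".

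The Analyses section of the resident evaluation then sets out the adjustment in three steps:

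- Baseline characteristics, including demographic factors and the outcome measures themselves, "will be investigated using independent samples t-tests".
- What the tests find feeds the model: "Any differences identified may be considered as covariates in the main analyses".
- A candidate list follows: "Covariates may include age, gender, building site, functional ability, car ownership, socio-economic status or other demographic variables that differ between residents".

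The main analysis is described by its target: "We intend to run a difference-in-difference analysis to test for differences between intervention and control groups in change from baseline to 3-6-month post-move-in", and likewise to the later follow-up. Continuous outcomes get linear regression and categorical outcomes logistic regression. The power statement for physical activity gives 107 participants for 80% power at α = 0.05, with five main predictors and three covariates. It does not name the five predictors, the three covariates or the effect size.

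**The concern.** In a non-randomised comparison a variable needs adjustment if it differs between groups and predicts the outcome of interest, which here is change. A baseline p-value addresses only the first condition, and addresses it badly at this sample size. An imbalance can be large enough to bias the result and still not be significant. Which variables enter the adjusted model also becomes known only after the data are seen. The list names six kinds of candidate, the power statement allows three, and nothing says which three.

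The second issue is what an included covariate can do. Difference-in-difference already removes group differences in level that are additive and constant over time. What it does not remove is a difference in trend, for example if older or less able residents decline faster and the groups differ in age or function. A covariate helps with this only if the model lets it explain change. If it does not, a report could present an adjusted effect that equals the unadjusted one.

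**Working it through.** **1. The plan's own figure.** Inputs from the power statement: N = 107, 5 + 3 = 8 model terms, α = 0.05. The effect size is not given, so f² = 0.15 is an assumption. For an overall F test, the noncentrality is λ = f²N = 0.15 × 107 = 16.05, with 8 and 107 − 8 − 1 = 98 degrees of freedom. Power is 79.5%, and 109 participants are needed for 80%. The stated 107 is therefore closely reproduced; exactly 80% at 107 needs f² = 0.152. At the same f² = 0.15, testing five of the eight terms needs 92 participants and testing two of the eight needs 68.

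**2. Power of the screening test.** The 53/54 split is assumed, because no allocation ratio is stated. The noncentrality of the t statistic is d × √(53 × 54 / 107) = 5.172d, on 105 degrees of freedom, two-sided 5%.

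| Imbalance d (SD) | Noncentrality | Probability flagged |
|---|---|---|
| 0.2 | 1.034 | 17.6% |
| 0.3 | 1.552 | 33.7% |
| 0.4 | 2.069 | 53.6% |
| 0.5 | 2.586 | 72.6% |

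A variable that differs by 0.3 SD, and whose inclusion depends on the test, is missed with probability 1 − 0.337 = 0.663, about two times in three. Gender, ethnicity and marital status, listed under Measures, are categorical, so a comparison of means is ill-suited to them.

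**3. What the predictor count suggests.** With baseline and two follow-ups, a stacked model has one group term, two visit terms and two group-by-visit terms, which makes five. Three covariates at one term each are main effects. This matches the power statement, but the article does not state it.

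**4. What main effects do in that model.** The group-by-visit part fits a separate mean for each group at each visit. Given a covariate slope b, each fitted cell is its outcome mean minus b times its covariate mean. With complete panels and a covariate X that does not change over time, the covariate mean in a group is the same at every visit, so

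[(Ȳ_I1 − bX̄_I) − (Ȳ_I0 − bX̄_I)] − [(Ȳ_C1 − bX̄_C) − (Ȳ_C0 − bX̄_C)] = (Ȳ_I1 − Ȳ_I0) − (Ȳ_C1 − Ȳ_C0).

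The covariate cancels. In a change-score regression of ΔY on group and X, the group coefficient is instead the difference in mean change minus c(X̄_I − X̄_C), where c is the slope of change on X. There the covariate does adjust.

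**5. Numerical check, with invented inputs.** Simulated complete panels, n = 107, true effect 0, a covariate shifted by 0.6 SD between groups and related to change at −0.4 per SD, so the expected bias is 0.6 × (−0.4) = −0.24. Means over 300 replicates:

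- unadjusted: −0.2505
- covariates as main effects: −0.2505 (largest difference in any replicate 9 × 10⁻¹⁵)
- covariate-by-visit terms: −0.0081
- change score with the same covariates: −0.0081

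**6. Where the identity stops.** In single simulated data sets, main-effect covariates moved the estimate from −0.466 to −0.452 with about 30% covariate-dependent dropout, from −0.089 to −0.153 with a time-varying covariate, and from −0.601 to −0.611 in a logistic model. Under dropout the mean over 200 replicates moved only from −0.2237 to −0.2226, so the bias stayed.

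**The case against.** The strongest reply is that the article does not state the stacked main-effects model. Its wording, group differences in change from baseline, fits a change-score regression, in which baseline covariates do adjust. The 107 is also reproduced with one row per person, whereas three stacked waves would give 3 × 107 = 321 rows. So the predictor count points one way and the sample size the other. The form of a covariate is also something an article commonly leaves to a fuller plan. This stands: the second part can only be conditional.

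A reader might infer that covariates can never change the estimate, or that the planned adjustment removes no confounding at all. Neither is supported. The identity needs a linear model, complete panels and time-invariant covariates. The plan includes logistic models, follow-ups only where possible, and functional ability, which can vary over time. The design itself deals with additive time-constant differences, and the Setting and residents section intends to match sites on demographics such as age and income.

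Nor are the t-tests shown to be the only gate. The rule is permissive, and the closing condition, "other demographic variables that differ between residents of intervention and control sites at baseline", may qualify only the last item of the list, so age or car ownership could enter whatever their p-values. That weakens the two-in-three figure for the named variables. It does not rescue the rule, because the list is itself optional and open-ended and the choice is still left until the data are in.

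On cost, three covariates interacted with two follow-up visits add 3 × 2 = 6 terms, making 14. On the overall-F basis with f² = 0.15 assumed, that needs 135 participants, or gives 66.1% power at 107. But the difference-in-difference question concerns the two group-by-visit terms. For those, on the same assumption, the requirement goes only from 68 to 69. The change-score form needs no covariate-by-visit terms.

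**Conclusion.** The point holds in two parts of different strength.

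The first rests on the text. Covariate choice in a non-random comparison is linked to baseline significance tests that would flag a 0.3 SD imbalance about one time in three and a 0.5 SD imbalance about 73% of the time, given the assumed near-equal split. The resulting adjusted model is data-dependent.

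The second is conditional. If the power statement means a stacked linear model with covariates as main effects, then with complete data and time-invariant covariates the adjusted and unadjusted estimates coincide, and confounding of trends remains. If a change-score model is intended, one sentence saying so settles it, and only the first part needs correcting.

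The size of any bias in this study cannot be derived from the article, which gives neither the imbalances nor how the covariates relate to change. The simulated figures show only how the models behave.

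**What to change.** Four changes to the analysis wording:

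- Remove the baseline t-tests as a route to covariates, and describe balance with standardised differences.
- Name a small covariate set in advance, on subject-matter grounds, from variables already collected. Examples are age, gender, baseline functional limitation from the two SF-12 items, car access and socio-economic status. Use it whatever the baseline p-values.
- State that covariates act on change, through a change-score regression or covariate-by-visit terms.
- If covariate-by-visit terms are chosen, update the predictor count in the power statement and say which terms are tested.

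No new data are needed. The cost is the wording and a few degrees of freedom.

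### The difference-in-difference model names no resident-level term for repeated visits, and the power rule should be confined to the choice between sampling single residents and couples

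*Protocol article*

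**What the plan says.** All the relevant text is in the protocol article, Quantitative resident evaluation.

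- **Estimand (Analyses).** The analysis will "test for differences between intervention and control groups in change from baseline to 3-6-month post-move-in", and likewise for change to the 9-12-month visit.
- **Model (Analyses).** The regression type follows the outcome: "linear regression for continuous outcome variables, logistic regression for categorical outcome variables". The power statement describes a model with "five main predictor variables and three covariates".
- **Visits (Procedures).** Each resident has one baseline measurement and, if possible, two follow-ups.
- **Clustering (Analyses).** Subject to the number of units at the final sites, "data may be collected on couples and a multi-level modeling approach used to control for clustering within unit". The next sentence is the selection rule: "The approach that is best able to maximize power will be chosen".
- **Eligibility (Participants).** Every adult living in an independent living unit is invited. No limit of one resident per unit is stated.

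The section mentions no resident-level effect, robust variance or change-score outcome.

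**The concern.** Two kinds of dependence can arise in these data, and the text secures neither.

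The first is between visits of the same resident. A pre-post design gains its precision from comparing each resident with himself or herself. A regression that treats the visits as independent observations gives the right point estimate in balanced data, but leaves the stable differences between residents in its error term. The test becomes conservative and loses power.

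The second is between two residents of the same unit. Here the error runs the other way: ignoring positive correlation makes the standard error too small. A model that ignores it therefore looks more powerful than one that respects it. For that reason power cannot be the criterion for deciding whether the dependence is modelled, although it is a fair criterion for deciding whom to sample.

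At stake are the power and the type I error of the primary physical activity comparison.

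**Working it through.** **1. The plan's own figure.** The article states "a difference-in-difference linear regression analysis with a continuous outcome will have 80 % power with 107 participants". It gives no effect size, so f² = 0.15 is an assumption. Take the overall F test of 5 + 3 = 8 terms, with noncentrality f² × N and error degrees of freedom N − 9. It needs N = 109 for 80% power and has 79.5% power at N = 107, which agrees within tolerance. Testing only five of the eight terms at the same f² would need N = 92. On this reconstruction, 107 counts independent observations and contains no allowance for clustering.

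**2. Which model do five predictors describe?** A change-score regression at one follow-up has one main predictor, group. A stacked model over three visits has group (1), visit indicators (2) and group-by-visit terms (2), and 1 + 2 + 2 = 5. This matches, but it is an inference.

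**3. Stacked visits with no resident-level term.** Assume total variance σ², n residents per group and the same correlation rho between any two visits of one resident. If covariates are in the model, rho is the correlation that remains after them.

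- Variance that ordinary regression assumes for the difference-in-difference: 4σ²/n.
- Actual variance: 4σ²(1 − rho)/n.
- Ratio of reported to actual standard error: 1/sqrt(1 − rho).
- Actual type I error: 2 × [1 − Φ(1.96/sqrt(1 − rho))].
- Actual power for an effect with 80% power under a correct model (1.96 + 0.84 = 2.80): 1 − Φ(1.96/sqrt(1 − rho) − 2.80).

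| rho (assumed) | SE ratio | Type I error | Power |
|---|---|---|---|
| 0.3 | 1.20 | 1.9% | 68% |
| 0.5 | 1.41 | 0.6% | 51% |
| 0.7 | 1.83 | 0.03% | 22% |

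Simulation (54 residents per arm, three visits, 4,000 runs) gave SE ratios of 1.38 and 1.79 at rho 0.5 and 0.7, and power of 50.5% and 22.9%. A change-score regression on simulated data without couples held type I error at about 5%. These factors are for the linear model.

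**4. Couples enrolled and the unit-level term omitted.** Design effect DE = 1 + ICC × share of residents in pairs. Type I error = 2 × [1 − Φ(1.96/sqrt(DE))]. The ICC is that of the change between two residents of one unit. The article gives none, so the values are assumed.

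| ICC | Share paired | DE | Type I error | 107 × DE, rounded up |
|---|---|---|---|---|
| 0.1 | half | 1.05 | 5.6% | 113 |
| 0.1 | all | 1.10 | 6.2% | 118 |
| 0.3 | half | 1.15 | 6.8% | 124 |
| 0.3 | all | 1.30 | 8.6% | 140 |
| 0.5 | half | 1.25 | 8.0% | 134 |
| 0.5 | all | 1.50 | 11.0% | 161 |

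A simulated change-score analysis that ignored a couple ICC of 0.3, with all residents paired, gave 8.0% to 8.8%. A change-score outcome therefore cures step 3 but not step 4.

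**5. The two errors do not add.** With stacked visits, rho 0.5 and an ignored couple ICC of 0.3, the simulated type I error was 1.5%: the conservative error dominates. The 7-11% applies when repeated visits are handled properly and couples are not.

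**The case against.** **Couples.** The clustering sentence joins enrolling couples to the multi-level model, and both hang on the number of units. Its natural meaning is a choice between one resident per unit with ordinary regression and couples with a multi-level model. Both are valid, and power may decide between them. A reader might infer that the article permits enrolling couples and then dropping the model, or choosing after the outcomes are seen. The text supports neither: the stated trigger is a feature of the buildings, and the decision concerns whether data are collected on couples. This objection largely stands. What remains is that the wording is permissive, does not require the multi-level term whenever two residents share a unit, and sets no date for the choice.

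**Repeated visits.** A reader might infer that the planned standard errors are far too large. The article never says that visits will be stacked without a resident term. Change from baseline to each follow-up also fits two change-score regressions, and a condensed article may leave covariance structure to an analysis plan. Nor would a rule to maximise power favour an analysis that loses it. All this makes the point conditional. It does not remove it: five main predictors do not describe a change-score model, a difference-in-difference by logistic regression is normally fitted to stacked visits, and the article does discuss clustering but names only the unit level.

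**Size.** Having all residents in pairs is an extreme case, especially with an expected participation rate of 50-55%, and shared stable household factors cancel from a change. The lower rows of the couples range may well be the relevant ones.

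**Conclusion.** The point holds in conditional form and is worth correcting. If the visits are stacked in ordinary linear regression with no resident-level term, the standard error of the primary contrast is 1.41 to 1.83 times too large for rho 0.5 to 0.7, and true 80% power falls to about 51% or 22%. This rests on the inferred reading of the five predictors and on assumed correlations. If couples are enrolled and their dependence is not modelled, type I error is about 7-11% for an assumed ICC of 0.3-0.5 with half to all residents paired. This is a smaller effect, and the natural reading of the article avoids it. The documents do not show that either error is planned. They show a model description that leaves the first open and a selection rule worded too broadly to exclude the second.

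**What to change.** - **State the model.** For continuous outcomes, use a linear mixed model with group, visit and group-by-visit and a random intercept for resident, or a change-score regression at each follow-up. For categorical outcomes, use a mixed or GEE logistic model with the same fixed terms.
- **Make the unit level mandatory.** Include a random intercept for unit, or a cluster-robust variance, whenever any unit contributes two residents.
- **Confine the power rule.** Let it govern only the choice between one resident and couples per unit, and make that choice before enrolment.

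The cost is a few sentences and no extra data. Intervals become slightly wider if couples are enrolled. Compared with a stacked ordinary regression, they become narrower because the within-resident correlation is used. Dependence within building sites is a separate question that these changes do not settle.
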